## Abstract

**Background:**

Suicide amongst Australian Aboriginal and Torres Strait Islander communities occurs at twice the rate of the general population and, with significant barriers to treatment, help-seeking prior to a suicide attempt is low. This trial aims to test the effectiveness of an app (iBobbly) designed with Aboriginal and Torres Strait Islander people for reducing suicidal ideation.

**Methods/design:**

This is a two-arm randomised controlled trial that will compare iBobbly to a wait-list control condition. The trial aims to recruit Aboriginal and Torres Strait Islander participants aged 16 years and over to test iBobbly, which is a self-help app delivering content based on acceptance and commitment therapy. The primary outcome for the study is suicidal ideation, and secondary outcomes include depression, hopelessness, distress tolerance, perceived burdensomeness and thwarted belonging, and help-seeking intentions. Data will be collected for both groups at baseline, post-intervention (after 6 weeks of app use), and at 6 months post-baseline (with a final 12-month follow-up for the iBobbly group). Primary analysis will compare changes in suicidal ideation for the intervention condition relative to the wait-list control condition using mixed models. An examination of the cost-effectiveness of the intervention compared to the control condition will be conducted.

**Discussion:**

If effective, iBobbly could overcome many barriers to help-seeking amongst a group of people who are at increased risk of suicide. It may provide a low-cost, accessible intervention that can reach more people. This trial will add to a sparse literature on indigenous suicide prevention and will increase our knowledge about the effectiveness of e-health interventions for suicide prevention.

**Trial registration:**

Australian New Zealand Clinical Trials Registry, ACTRN12614000686606. Registered on 30 June 2014.

**Electronic supplementary material:**

The online version of this article (10.1186/s13063-019-3262-2) contains supplementary material, which is available to authorized users.

## Background

Suicide intervention research is rare in Indigenous communities. While suicide rates for the general population in Australia have been relatively stable over the last 20 years, they continue to increase for Australian Aboriginal and Torres Strait Islander communities [1]. Despite a raft of policies, programs, and funding announcements aimed at suicide prevention for Indigenous Australians, suicide rates amongst Aboriginal and Torres Strait Islander people are currently twice that of the general population [2]. Against a history of dispossession, oppression, and disadvantage, suicide and help-seeking amongst Aboriginal and Torres Strait Islander people is different to what we see in the general population. In addition to a raft of structural issues such as poverty, social disadvantage, and poor physical health, there is a mistrust of mainstream services founded on a history of racism and mistreatment, a lack of services available to those in regional and remote areas, and a sense of shame. These issues are substantial barriers to treatment. Current initiatives are not achieving the desired outcome, with few Aboriginal and Torres Strait Islander people (hereafter respectfully referred to as Indigenous Australians) seeking help for their distress [3, 4] and even fewer finding effective services. Efforts directed at providing evidence-based help to those who don’t currently seek it are likely to reduce suicide rates.

Within the general population, reductions in suicidal ideation can be achieved using several face-to-face therapies, including cognitive behaviour therapy (CBT) [5], mindfulness-based CBT (MBCT) [6], and dialectical behaviour therapy (DBT) [7]. A recent iteration of CBT, acceptance and commitment therapy (ACT), has demonstrated effect sizes similar to those of traditional CBT, and superior effects to control conditions for a range of mental and physical health disorders [8]. ACT has demonstrated efficacy as a self-help intervention for chronic pain [9] and tinnitus [10] and as a prevention intervention for depression and anxiety symptoms [11]. An acceptance and emotional regulation-based intervention reduced self-harm in people with borderline personality disorder (BPD) [12]. Limited evidence shows that where ACT is being used in Indigenous communities it is acceptable and culturally aligned [13].

Web-based and self-help interventions have been found to reduce depression, anxiety, and suicide ideation, and may offer a solution to problems of service access and implementation [14–16]. In particular, apps downloaded to phones or mobile tablets then become available at all times, even without internet connection. Suicide prevention interventions offered via an app may have advantages by allowing people to seek help anonymously, compensating for a limited workforce, offering around-the-clock availability, and overcoming the stigma or shame barrier [3, 17]. An app is able to deliver interventions to a large number of individuals at a relatively low cost [18], and can be designed as an indicated preventively oriented intervention rather than as a response to crisis situations. When co-designed with young Aboriginal and Torres Strait Islander people, the chances of the intervention being unacceptable for cultural or age-related reasons can be expected to be much lower.

iBobbly is a self-help app developed to reduce suicidal ideation and plans. The app includes trans-diagnostic content from the most recent evolutions of cognitive behavioural therapy: ACT [19, 20], MBCT [6], and DBT [21]. The app was developed in consultation with Indigenous Australians and uses an ACT framework of values-based action, de-fusion from unhelpful thoughts, and acceptance of difficult emotions, drawing on values embedded within Indigenous culture. It was designed to be engaging and interactive whilst delivering an evidence-based therapy. iBobbly is designed to be accessible for people with lower literacy skills through the use of images, animations, and voice-overs created by Indigenous artists, graphic designers and speakers, and minimal use of text. Once downloaded the app also does not require the internet for ongoing use.

A pilot RCT of a prototype of the iBobbly app (version 1) was conducted in the Kimberley region of Western Australia between September 2013 and March 2015, involving 61 Indigenous participants aged 18–35 years. Participants were randomised to receive either the app, which delivered acceptance-based therapy over 6 weeks, or were waitlisted for 6 weeks and then received the app for the following 6 weeks. While the between-group changes in suicidal ideation from pre-intervention to post-intervention were not statistically significant, the pre–post intervention change for the iBobbly arm was statistically significant, showing a mean decline of 0.84 (95% CI 0.14–1.53) on the Depressive Symptom Inventory—Suicidality subscale [22]. This corresponds to a moderate effect size of 0.39 (Cohen’s d) and, in a preventive context, justifies further research using the app. In addition, participants in the iBobbly group showed substantial and statistically significant reductions in psychological distress compared with those in the waitlist. Change in impulsivity as measured in the trial was nonsignificant and negligible in size [23].

The current study differs from the pilot study in several ways. The major changes from the pilot study are the inclusion of several additional hypotheses (outlined below) and the inclusion of a cost-effectiveness analysis. This has resulted in additional outcome measures, including more comprehensive measures of suicidality, help-seeking, distress tolerance, interpersonal needs, service use, and quality of life. iBobbly itself is now a substantially different intervention, with major revisions based on feedback from the first pilot and from national consultations with a range of Aboriginal and Torres Strait Islander groups and communities. The study is recruiting a larger sample size from an additional five regions, representing a broader cross-section of Aboriginal and Torres Strait Islander communities. The lower age limit for participants has been reduced from 18 to 16. Finally, longer between-group (6 months) and intervention within-group (12 months) follow-up periods are included.

## Aims

### Primary aim

The primary aim of the trial is to test the effectiveness of the iBobbly app (version 2) compared to a waitlist control condition in reducing levels of suicidal ideation immediately post-intervention (6 weeks).

### Secondary aims

The secondary aims are as follows:▪ To test the effectiveness of the iBobbly app compared to a waitlist control condition in reducing levels of suicidal ideation 6 months post-baseline.▪ To test the effectiveness of the iBobbly app compared with the control condition for reducing symptoms of depression, hopelessness, perceived burdensomeness, and thwarted belongingness and for increasing quality of life, help-seeking intentions, and healthcare utilisation immediately post-intervention (6 weeks), and 6 months post-intervention.▪ To examine the 12-month outcomes for participants randomised to the iBobbly group.

### Subsidiary aims

Subsidiary aims include to examine predictors of outcomes and non-response to the intervention, adherence to the app, acceptability of the intervention, trial dropout, and the cost-effectiveness of the intervention compared to the wait list control group.

## Trial hypotheses

In accordance with the above aims, the project is driven by several hypotheses:▪ The iBobbly intervention will result in a reduction of suicidal ideation as measured by the Suicidal Ideation Attributes Scale (SIDAS) relative to the wait list control condition post-intervention (six weeks). The SIDAS is the primary outcome measure.▪ The difference in suicidal ideation (measured by the SIDAS) between intervention and wait list control will be maintained at six months.▪ For participants in the intervention group, reductions in suicidality will be maintained at the 12-month follow-up.▪ The intervention will result in a reduction of reported suicide intent and plans as measured by the Quick Inventory of Depressive Symptomatology (QIDAS) relative to the control group at six weeks post-baseline and at six months.▪ Relative to the wait list control condition, the intervention will lower symptoms of depression at six weeks post- baseline and six months.▪ An increase in quality of life and self-reported help-seeking intentions is expected from baseline to six-month follow-up following use of the app.▪ A reduction in suicidality (as measured by suicidal ideation, suicide plans and capacity to cope with suicide thoughts) will be associated with improvement in depression, improvement in burdensomeness and belongingness, improvement in distress tolerance, and greater program adherence.▪ The cost effectiveness analysis will result in a favourable incremental cost effectiveness ratio for the intervention group relative to the control wait list with an improvement in quality of life, with higher costs associated with use of iBobbly app and treatment seeking, but lower use of crisis health care and social services (such as presentations to emergency department and inpatient units).

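### The hypothesis on quality of life and help-seeking intentions names no comparator, which contradicts the controlled secondary aim and the planned between-arm analysis

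*Protocol article*

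**What the plan says.** **Hypothesis.** The protocol article, Trial hypotheses, states: "An increase in quality of life and self-reported help-seeking intentions is expected from baseline to six-month follow-up following use of the app". The list containing it opens with "In accordance with the above aims, the project is driven by several hypotheses".

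**Aim.** The corresponding item under Secondary aims begins "To test the effectiveness of the iBobbly app compared with the control condition for reducing symptoms of depression" and continues, within the same controlled comparison, "for increasing quality of life, help-seeking intentions, and healthcare utilisation immediately post-intervention (6 weeks), and 6 months post-intervention".

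**Neighbouring hypotheses.** Depression is worded "Relative to the wait list control condition, the intervention will lower symptoms of depression". The cost-effectiveness hypothesis expects a "favourable incremental cost effectiveness ratio for the intervention group relative to the control wait list with an improvement in quality of life". The hypotheses on SIDAS at six weeks and six months and on suicide intent and plans also name the control arm.

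**Analysis.** Under Statistical analysis, Analysis plan, continuous secondary measures get the same kind of mixed model as the primary outcome, to assess whether change differs by arm. A later part of that section says that 6-month data enter separate analyses. It then says that change can be estimated in the active group and in the wait-list group once it has used the app, but that there can be no comparison with untreated participants.

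**Wait-list.** Methods/design describes a 6-month wait-list and a follow-up 6 months after baseline. Procedure has control participants receive the tablet and app 6 months after the intervention group.

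**The concern.** The hypothesis is met by a rise from baseline among people who have used the app. At six months those people are in the intervention arm only. A rise in that arm can come from the app, from regression to the mean, from the passage of time, or from the service information, referral and wellbeing checks that both arms receive. Only the randomised comparison separates the app from the rest, and the design provides one at that visit.

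The aim and the hypothesis therefore define success differently for the same two outcomes. If both wordings stand, the report could describe the hypothesis as supported on a pre-post change even where the arms do not differ. The choice between the two definitions could also be made after the results are known.

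**Working it through.** **1. The statements side by side**

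| Place | Outcomes | Comparator |
|---|---|---|
| Secondary aims | quality of life, help-seeking intentions | control condition |
| Trial hypotheses, this item | quality of life, help-seeking intentions | none; change from baseline |
| Trial hypotheses, cost-effectiveness item | quality of life within the economic comparison | wait-list |
| Analysis plan, secondary measures | continuous/scaled secondary measures | other arm |
| Analysis plan, 6-month remarks | not specified by outcome | within-group; untreated comparison ruled out |

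The hypotheses are said to follow from the aims, so the first two rows should agree. They do not.

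**2. Is there an untreated comparator at six months?** The wait lasts 6 months and the visit is 6 months after baseline. Provided the assessment is completed before the app is handed over, the control arm has not used it. The Analysis plan's remark about wait-list change after app use can therefore describe only later data, yet it is attached to the 6-month follow-up. (The aim counts its last time point from the end of the intervention. I take it to mean the visit 6 months after baseline, the only 6-month visit in Methods/design.)

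**3. The plan's own figure.** Inputs from Sample size and power calculations: d = 0.28, correlation r = 0.5, two-sided alpha 0.05, power 0.80, dropout 30%.

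- SD of change = SD × √(2(1 − 0.5)) = 1.0 SD.
- n per arm = 2 × (1.960 + 0.842)² / 0.28² ≈ 200.2, rounded up to 201. The t-based calculation gives 201.2, rounded up to 202.
- 202 / 0.70 = 288.6, rounded up to 289.

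The stated 202 and 289 reproduce. These are for SIDAS at 6 weeks; no figure is given for quality of life or help-seeking.

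**4. Illustration of the literal reading.** Assume no app effect, both arms improving by d baseline SDs, and m = 202 completers in the app arm. A paired t test has noncentrality d × √m / √(2(1 − r)) on 201 degrees of freedom. At d = 0.20 and r = 0.5 this is 0.20 × 14.21 / 1.0 = 2.84. The probability of a significant improvement is:

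| Shared improvement (SD) | r = 0.3 | r = 0.5 | r = 0.7 |
|---|---|---|---|
| 0 | 0.025 | 0.025 | 0.025 |
| 0.10 | 0.222 | 0.293 | 0.447 |
| 0.15 | 0.434 | 0.564 | 0.782 |
| 0.20 | 0.667 | 0.808 | 0.955 |
| 0.28 | 0.917 | 0.977 | 0.999 |

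The between-arm test stays at 0.025 in favour of the app (0.05 two-sided) in every row, because a shared improvement cancels.

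**The case against.** The strongest reply is that no uncontrolled test is actually specified. The hypotheses are tied to the aims, the aim is controlled, the model for secondary measures assesses differential change, and quality of life also appears in a hypothesis set against the wait-list. On that view one item has merely lost its comparator. Much of this stands: if the differential-change analysis is followed, shared improvement will not produce a positive result. A reader might infer that the trial plans to judge these outcomes on pre-post change alone; the documents do not support that. The reply does not fully settle the matter, because the 6-month remarks in the Analysis plan point the other way at this hypothesis's only time point.

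Three further inferences should be resisted.

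- **The 12-month hypothesis.** "For participants in the intervention group, reductions in suicidality will be maintained at the 12-month follow-up" is also within-arm, but openly so. It agrees with the secondary aim to examine 12-month outcomes in the iBobbly group, with the Background, and with Community consultation. The wait-list arm has been given the app by then, so no untreated comparator can exist. It is not an inconsistency.
- **The pilot.** The Background reports that "the pre–post intervention change for the iBobbly arm was statistically significant, showing a mean decline of 0.84", while the between-group difference was not significant. That is an app-arm change on a suicidality subscale and includes any app effect. It says nothing about natural drift in quality of life or help-seeking intentions.
- **Enrolment at a low point.** The eligibility criteria set no minimum level of ideation or distress and exclude active suicidality. Marked spontaneous improvement cannot be presumed.

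**Conclusion.** The point holds as an internal contradiction. The hypothesis is worded as an uncontrolled increase, while the secondary aim and the main analysis text treat the same outcomes as a comparison of arms, and the 6-month remarks leave the weaker reading available. Taken literally, improvement common to both arms would confirm the hypothesis.

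The consequence is limited to what may be concluded about two secondary outcomes. The primary hypothesis, its analysis and the sample size do not change.

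The false-confirmation rates, such as 81% at 0.20 SD (67% to 96% for r from 0.3 to 0.7), are an illustration and not a forecast. They rest on an assumed drift, on a correlation and completer count borrowed from the SIDAS calculation at 6 weeks, and on a test that the plan does not specify for these outcomes.

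**What to change.** 1. Reword the hypothesis to say that the intervention will increase quality of life and help-seeking intentions from baseline to six months relative to the wait-list control, tested by the arm-by-time contrast at 6 months in the mixed model already planned for secondary measures.
2. In the Analysis plan, confine the statement that an untreated comparison is impossible to data collected after the wait-list arm receives the app, and state that the 6-month visit is a between-arm comparison.

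The cost is one phrase and one sentence. The data, model and comparator are already in the design, so nothing is added to assessments, sample size or the primary analysis.

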## Methods/design

A two-arm randomised controlled trial (RCT) will be conducted (one active intervention/one 6-month wait list control) using three measurement occasions: baseline, post-intervention (after completing the program at week 6), and follow-up at 6 months after baseline assessment. After community consultation, the waitlist control condition was selected as the only acceptable one to the Aboriginal and Torres Strait Islander communities involved in the trial. A SPIRIT checklist (Additional file 1) was completed to address all necessary items in the trial protocol.

### Community consultation

Following consultation with Aboriginal community members during research design it was decided that to ensure ethical standards and maintain appropriate duty of care, all participants would be provided with information about crisis services and offered referral to clinical services if needed. As such the study examines the impact of iBobbly compared to usual care in the waitlist group. The age range for recruitment was initially 16–35 years; however, following commencement of recruitment, feedback from research sites indicated that many community members over the age of 35 wished to take part and would likely benefit from the app; so to maintain positive relationships with community the upper age limit was removed. The initial follow-up period was to be 24 months but given difficulty with recruitment and feedback regarding burden of numerous follow-up questionnaires the 24-month follow-up was removed with the 12-month remaining as the final follow-up point for the iBobbly group.

### Recruitment

Community-dwelling Indigenous individuals will be recruited to this study via advertisements on social networking sites, Indigenous media, community events, and through established relationships with Aboriginal community health services.

Participants will be recruited from six regions across four Australian jurisdictions: Broome (Western Australia); Darwin (Northern Territory); Darling Downs (Queensland); and Hunter New England, La Perouse, and the Murrumbidgee region (New South Wales).

Eligibility to take part in the trial is determined in a stepwise screening process. To be eligible, participants must:▪ Be at least 16 years of age▪ Be of Aboriginal or Torres Strait Islander descent▪ Be a resident of Australia and reside within an ethics-approved region (listed above)▪ Have the ability to navigate a basic app▪ Not be actively suicidal▪ If diagnosed with a psychotic disorder such as schizophrenia not be currently experiencing symptoms▪ Be willing to contact the Suicide Call Back Service (SCBS) if needed▪ Be able to understand spoken English

### Randomisation

Randomisation of participants will occur with equal probability for both groups. Participants will be stratified based on gender (male/female) and severity of suicidal thoughts calculated from the SIDAS [24], using a cut-off score of 21 (subthreshold/high risk). Randomisation will be carried out at the Black Dog Institute by the trial manager using automated randomisation software for block randomisation (four per block). Participants were aware of allocation as they were provided the tablet with the app if randomised to the iBobbly group.

### Procedure

Upon recruitment, participants will be screened over the telephone or face-to-face using brief questionnaires to establish eligibility as per the criteria above. Participants will be excluded from the trial if they present with active suicidality at the time of recruitment, as indicated by a current plan to harm themselves or reporting having taken steps to put a suicide plan into place. These respondents will receive appropriate referral information to health services and crisis lines and will be supported to seek help (Fig. 1). Participants excluded on the basis of a diagnosis of schizophrenia or another psychotic illness will also be provided with referral information. To accommodate participants with varying literacy skills, individuals who meet the inclusion criteria will be given the option to complete baseline and follow up measures face-to-face or through a telephone interview with a site coordinator or the trial manager, or online.

